### Application testing

At this stage, the unit test of the final application will be performed by researchers and different modules of the application will be tested separately to confirm correct performance, which can help to eliminate any potential defects. In the next step, application integrity test will be performed by researchers. For this purpose, one researcher will put him/herself in the position of the patient and another researcher in the position of the physician. Feedback on probable defects of the application will be given to application designers.

### Implementation and evaluation of application in the live environment (clinical trial)

#### Study design and setting

At this stage, an interventional study will be conducted through patient blinding by an assessor physician and analyst to evaluate the effects of the application on patient self-care. The designed application will be installed on patients’ smartphones and the necessary training to use it will be given to the patients and their caregivers. This application will support Android 5 and above. The study population will include patients referring to one of the general hospitals in Kashan where sampling can be done in a convenient way. Patients with hemiplegia or hemiparesis caused by a recent stroke will be chosen for this purpose. Either the patient or his/her patient caregiver must have an Android-based smartphone and be able to work with it. At least 72 h must have passed since the stroke (The acute phase of the disease must have passed) and patients must have adequate consciousness and hearing and be willing to participate in the study. Exclusion criteria will include:Patients who have some levels of consciousness disorderPatients with cognitive disorders such as dementia or memory impairmentPatients with global aphasia

The formula “n = [(Z_1−α/2_ + Z_1−β_)^2^ * (σ_1_^2^ + σ_2_^2^)]/($$\overline{x }$$_1 _− $$\overline{x }$$_2_)^2^” with the reliability of 95% and the test power of 90% based on the mean and standard deviation of baseline NIHSS obtained in the same study [29] (Z_1−α/2_ = 1.96, Z_1−β_ = 1.282, σ_1_, σ_2_ = 8, $$\overline{x }$$_1_ = 5, $$\overline{x }$$_2_ = 12) was calculated as 27 patients, which increased to 30 patients according to the available facilities which, with a 10% sample dropout, will increase to 33 individuals. Accordingly, two groups each including 33 patients (intervention and control) with stroke (66 patients in total) who meet the inclusion criteria will be selected.

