**Discussion:**

The assessed outcomes will include stroke severity using National Institute of Health Stroke Scale (NIHSS) score, ability to perform activities of daily living using Barthel Index (BI) score, depression rate using Beck Depression Inventory (BDI-II) score, quality of life using EQ-5D-3L score, medication adherence using Modified Morisky Medication Adherence Scale (MMAS-8) score, patient satisfaction using Patient Satisfaction Questionnaire (PSQ) score and the number and type of complications in patients in two groups. These outcomes will be assessed at baseline, after two months and after three months from the beginning of the intervention. Intervention effects on the measured variables will also be evaluated using appropriate statistical tests based on the type of variable distribution. Potential consequences of the study might be the improvement of the measured variables in the intervention group compared to that of the control group. The expected results are that the intervention may significantly improve the status of the measured variables in the intervention group compared to that of the control group. If the outcomes of the intervention group do not change significantly compared to those of the control group, it can be due to different reasons. However, this can most likely be attributed to incorrect or insufficient use of the application by patients.

*Trial registration*: This protocol is registered in the Iranian registration of clinical trial (IRCT) on November 7, 2020 with the code IRCT20201015049037N1. URL: https://irct.ir/trial/51674

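### The sample size rests on a 7-point NIHSS difference described as baseline values, so the stated 90% power is not shown to be power for an effect of the app

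*Protocol article*

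**What the plan says.** Study design and setting gives the usual two-mean formula with two-sided 5% significance (Z = 1.96) and 90% power (Z = 1.282). It describes the inputs as follows: "the test power of 90% based on the mean and standard deviation of baseline NIHSS obtained in the same study". The values entered are means 5 and 12 and SD 8 in each group. The article does not say which groups or time points the two means belong to. The result "was calculated as 27 patients, which increased to 30 patients according to the available facilities", and a 10% dropout allowance then takes it to 33 per group, 66 in total. The abstract (Methods) gives 60 patients, and Randomization provides 15 blocks of four, which is also 60.

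The Intervention section calls this a superiority trial of the app added to usual care. Outcomes are measured before the intervention and at two and three months. The abstract's Discussion allows that a null result could have various causes, then adds that "this can most likely be attributed to incorrect or insufficient use of the application by patients".

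**The concern.** The denominator of the formula should hold the between-group difference that the trial expects, or wants to be able to detect, after the intervention. The article puts there a difference that it labels baseline. Such a difference exists before anyone has been treated, so it cannot estimate what the app does. Between randomised arms of one trial its expected value is zero.

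No other part of the article supplies the missing link. Seven points is 7/8 = 0.875 SD, and it is not called expected, plausible or clinically relevant. By the article's own NIHSS bands, medium stroke runs from 5 to 15, so 7 points spans most of a severity class. The comparator is usual care that may already include physiotherapy or occupational therapy, and the Background cites studies in which such apps made no significant difference.

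This is the only power justification in the article. A reader who takes 90% at face value will think that a non-significant result tells more against smaller effects than it does, and the abstract ranks insufficient use first among the explanations.

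**Working it through.** **1. The plan's own figure.** Inputs, all from Study design and setting: Z = 1.96 and 1.282, SD 8 in both groups, means 5 and 12.

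n = (1.96 + 1.282)² × (8² + 8²) / (12 − 5)² = 10.5106 × 128 / 49 = 27.46 per group.

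The article prints 27. Rounding up would give 28, but this has no consequence because the number was raised to 30. Dropout: 30 × 1.10 = 33, as stated.

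**2. What the 90% refers to.** It is the power if the true difference in the compared NIHSS scores is 7 points with SD 8. The article ties neither figure to follow-up.

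**3. Power for other differences.** The documents give no app-versus-control difference and no follow-up SD, so the values below are illustrative assumptions. Method: two-sided 0.05 two-sample t-test with noncentrality δ / (SD × √(2/n)). SD 6 is included because the 8 comes from the same baseline source and need not be the SD at follow-up.

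| Analysed per arm | SD | Power for 4 points | Difference detectable with 90% power |
|---|---|---|---|
| 30 | 8 | 48% | 6.8 |
| 30 | 6 | 72% | 5.1 |
| 27 | 8 | 44% | 7.2 |

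At 30 per arm and SD 8, power is 91.5% for 7 points, 81.5% for 6, 66% for 5, 30% for 3 and 16% for 2.

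**4. Why 27 and 30 both appear.** If 66 are randomised and 10% drop out, 33 × 0.9 = 29.7, or about 30 per arm. If 60 are randomised, as the abstract and Randomization provide, 30 × 0.9 = 27 per arm.

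**5. Precision.** At 30 per arm and SD 8, the expected 95% CI half-width is t(58) × 8 × √(2/30) = 2.002 × 2.066 = 4.1 points.

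**The case against.** **The word baseline may be a slip.** The cited study is not at hand, and 5 and 12 could be follow-up values, or one a starting value and the other a target. This stands as a limit on certainty: one cannot assert that the two means are in fact a baseline gap between two groups. It does not rescue the text. If the label is wrong it must be corrected, and 7 points would still need support as an effect of this app.

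**The arithmetic is right.** Agreed.

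**The power figures depend on inputs that are themselves uncertain.** This also stands. SD 8 has the same baseline source. The number analysed depends on the unresolved 60 or 66. The Data analysis section leaves NIHSS out of its list of t-test outcomes and also plans a repeated-measures ANOVA with covariates, which could change the power. That is why a range is shown and not one corrected figure. The 90% claim cannot lean on the adjusted analysis, because the sizing formula is unadjusted and no correlation is stated.

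**Stronger readings that the documents do not support.** A reader might infer that lack of power is at least as likely as low use to explain a null result. The documents give no true effect from which to judge that. A reader might also infer that a null would be uninformative. With a half-width of about 4.1 points at SD 8, an estimate near zero would exclude a 7-point benefit. Nor does the abstract attribute a null to non-use alone: it allows other causes, and the main Discussion lists several for comparable studies. The Discussion also calls the sample relatively small, but only when speaking of generalisability.

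**Conclusion.** The point holds as a fault in the stated basis of the sample size. The trial is sized on a 7-point NIHSS difference that the article describes as baseline and nowhere justifies as a treatment effect at two or three months. The 90% power is therefore conditional on a true follow-up difference of about 7 points with SD 8.

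Under the illustrative assumptions, the difference detectable with 90% power lies between 5.1 points (30 per arm, SD 6) and 7.2 points (27 per arm, SD 8). At 30 per arm, power for 4 points is 48% at SD 8 and 72% at SD 6. No single corrected sample size follows, because the documents give neither a target difference nor a follow-up SD.

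The abstract's ranking of insufficient use as the most likely cause of a null has no support in the article. Limited power for smaller effects belongs beside it as a possibility, with no claim about which is likelier.

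**What to change.** 1. In Study design and setting, state what 5 and 12 are (groups and time point), and stop presenting a baseline difference as the effect.
2. Restate the power as conditional on an assumed difference in NIHSS at a named follow-up time and an assumed SD, shown as a range. For example: with 30 analysed per arm, 90% power for 6.8 points at SD 8 or 5.1 at SD 6; power for 4 points 48% and 72% respectively.
3. Before printing those figures, reconcile the 60 patients in the abstract and Randomization with the 66 in Study design and setting. If 60 are randomised with 10% dropout, the SD 8 figure becomes 7.2 points.
4. In the abstract, replace the sentence on the likely cause of a null result. Say that a non-significant result will be reported with its estimate and 95% CI, and that limited power for smaller effects is one possible explanation alongside low use.

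The cost is wording in the protocol and, where it repeats these statements, the registry entry, and a less favourable power statement. No extra patients are needed.

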#### Randomization

Randomization will be done by block method (Permuted Block Randomization) in a way that first all foursome blocks which include two codes A and B will be prepared (6 blocks) and then, using a table with random numbers, random blocks will be selected by placement (15 blocks). These blocks will contain up to 60 codes including A and B, each of which will be randomly assigned to either the control or the intervention group. This table will be generated by MS Excel 2019 and function of RANDBETWEEN (1,6).

#### Blinding

For the purpose of blinding, an application will be installed on the smartphones of patients of both intervention and control groups. The program installed for patients in the control group will only contain online questionnaires that patients need to complete and submit at specified intervals. Online questionnaires will include a number of questions used to measure the target variables. However, the program installed on the phones of participants in the intervention group will include all the capabilities and requirements of the self-care program designed in the design phase. Patients will not be familiar with the nature and content of the installed program on the opposite group’s phones. During program installation, someone other than the assessor physician will install the program for patients or their caregivers. Furthermore, during the assessment process, the same person will record the results of the physician evaluation and the scores related to each patient. Therefore, the assessor physician will not know which group a given patient belongs to. Numeric codes for intervention and control groups will also be used for analysis, and the letters A and B will be used for the control and intervention groups when information is sent to the analyst.

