**Methods:**

The first stage will include the development of an android-based application using JAVA programming language for developing the user interface and ASP.NET Core for developing Web server. The second stage will be conducted using triple blinded randomized clinical trial (RCT). The sample size will include 60 patients with recent stroke and partial paralysis of limbs, who will be divided into two groups of intervention and control through permuted block randomization method. Patients in both groups will receive usual medical care, but those in the intervention group will also use an Android-based application for a period of two months. Outcomes will be assessed using valid and reliable questionnaires.

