#### Data collection

The required data will be collected using valid and reliable questionnaires that are introduced as follows. Data will be collected in three stages: prior to intervention (before the intervention and at the time of discharge), two months after the intervention and three months after the intervention (in the doctor's office or in the hospital outpatient clinic). Data from National Institute of Health Stroke Scale (NIHSS) and Barthel Index (BI) questionnaires and stroke complication checklist will be filled out by the attending neurologist and other questionnaires will be filled out by patients as self-report. Completion of questionnaires by patients will be done electronically and sent online through the application. Therefore, this survey will be considered as a “closed survey” since only registered users with a valid account can access the questionnaires and submit them. Application features will be inactive until patients, complete questionnaire items. After completion, application features will be activated and the questionnaire will be deactivated to prevent response duplications. The questionnaires will be reactivated two months and three months later. In order to ensure that no data will be missing, all fields and questions will be defined as mandatory in electronic questionnaires and patients will be warned to answer all questions before sending the questionnaire.

All online questionnaires will exactly be designed the same as paper questionnaires in terms of appearance, content and sequence of questions. That is, all the questions will be placed consecutively and not on separate pages. Therefore, it can be said that the validity and reliability reported for the paper version of questionnaire will also apply to the electronic version.

It is expected that the use of this application can improve the measured variables in the intervention group compared to the control group. Specifically, the research hypotheses are that patients in the intervention group have significant differences with those in the control group in terms of indicators of physical activity, depression, quality of life, medication adherence, satisfaction with treatment, and the number of complications.

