## Discussion

Various protocols have been designed to evaluate the impact of mobile applications and trainings on the outcomes of patients with stroke [44–47]. However, these studies differ in terms of sample size, number of variables and outcomes to be measured, duration of intervention and protocol design. In Iran, a study in which first an application is designed using expert and patient needs assessments according to a standard guideline and then the impact of designed application on patients with stroke is evaluated has not been done yet. In other foreign studies, less attention has been paid to different aspects of ICF. However, in the present study, we will try to evaluate the outcomes based on valid and reliable questionnaires that are related to different sections of ICF.

In addition to providing educational materials via text and image, the application will provide appropriate exercises using educational video clips. It will also contain items such as reminders and warnings to take medications and doctor's appointments, the possibility of communicating with the therapist via chats, voice calls or video calls, the possibility of weekly goal setting, and writing notes related to the rate of goal achievement. It is expected that the use of this application will potentially improve and enhance the motor function of the upper and lower limbs, balance and walking, social participation and self-efficacy in the intervention group more than those of the control group. In similar studies [48–50], the positive effects of mobile applications on improving the motor function of limbs after stroke have been shown. However, some other studies [51, 52] have reported the use of this type of intervention on the motor function of the limbs without significantly improved effects. The reasons for this difference can be related to various factors such as the context of the society under study, the mobile application used and its capabilities, the duration of the intervention and the level of patient cooperation to use the application.

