The most important limitation of this study is the possibility of lack of cooperation of some patients to participate in the study. Researchers will understand the specific conditions of patients with stroke and will fully explain the purposes of the study to them, but in any case, if patients, despite being informed about the goals and efforts of researchers to obtain their satisfaction, seem to be unwilling to participate in the study, according to the principle of informed and free consent, they will be excluded from the study at any time during the research. Another limitation is the lack of qualified patients at the study site, which will probably make the sampling longer, but will not harm the results of the study. However, larger trials with larger samples in centers with more patients are recommended. One of the operational problems in studies of this type is the possibility of patients not being able to work with smartphones. If the patient is not able to work with a smartphone, his/her caregiver will be consulted. Of course, this person needs to be someone such as a patient’s wife/husband or child who is always available to the patient.

It can be said that the most important strength of this trial is the development of an application based on the needs assessment of all stakeholders. This can be a great advantage over studies that use an off-the-shelf application because it will be designed and adapted to the needs of the population under study.

The ability to generalize the results of the study to similar populations should be somewhat cautious. Although the sample at of this study is based on the formula and data obtained from previous studies, it is nevertheless a relatively small sample. Therefore, the generalizability of the results of this study needs to be done with caution.

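### The triple-blind label is not secured by the design: the person who records the physician's scores knows the arm, and patients can probably infer theirs

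*Protocol article*

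**What the plan says.** The article's title and the Methods part of its abstract claim triple blinding ("The second stage will be conducted using triple blinded randomized clinical trial (RCT"). The procedures behind the claim are spread over several sections.

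- **Installer and recorder (Blinding).** Each patient gets one of two programs, and "someone other than the assessor physician will install the program for patients or their caregivers". Then "during the assessment process, the same person will record the results of the physician evaluation and the scores related to each patient". The section concludes from this that the assessor will not know the group.
- **Rater (Data collection).** NIHSS, the Barthel Index and the complications list come from one clinician: the "stroke complication checklist will be filled out by the attending neurologist". The remaining questionnaires are patient self-reports sent through the app.
- **Patients (Blinding, Intervention).** The stated protection is that patients do not know what the other group's program contains. The control program holds questionnaires only. The other arm is advised to use a full self-care app 1 h a day, 5 days a week, for 8 weeks.
- **Analyst (Blinding, Randomization, Data analysis).** Blinding says "the letters A and B will be used for the control and intervention groups when information is sent to the analyst". Randomization says the two letters are allotted to the arms at random. Data analysis says only one researcher, who is neither assessor nor analyst, can decode the data. The same section plans to relate usage duration to the outcomes.

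**The concern.** A triple-blind label tells readers that patients, assessors and analysts could not act on knowledge of the arm. Here the person who writes down the physician's results has handled the arm-specific app. The article offers this arrangement as the reason the assessor stays blind. It does shield the assessor, but it places an arm-aware person between the rating and the database.

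Patients' ignorance of the other program is also weak protection when their own program has no self-care content. A control patient who consented to a study of a self-care app and finds only questionnaires has an obvious clue. Four outcomes are then reported by that patient, and depression, quality of life and satisfaction are the kind of self-report that expectation can influence.

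At stake is the credibility of any positive result: three outcomes are open to influence through the recorder and four through the patient. A reader who trusts the label would discount that possibility.

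**Working it through.** The point is mainly a comparison of sections; arithmetic only illustrates scale.

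**1. Who knows the arm, by role**

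| Role | Text | What follows |
|---|---|---|
| Installer | Blinding: handles two different programs | Knows the arm |
| Recorder of physician scores | Blinding: the same person | Knows the arm |
| Rater | Data collection: attending neurologist fills out the forms | Conflicts with Blinding on who writes the score; knowledge of the arm not stated |
| Patient | Intervention: questionnaires only, against about 5 h a week of self-care content | Can probably infer the arm |
| Analyst | Blinding lists A and B beside control and intervention; Randomization and Data analysis say random letters and a withheld key | Ambiguous on the letters; usage data could reveal the arm |

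In Blinding, the same person can sensibly mean only the installer, since the sentence is given as a reason for the assessor's ignorance. Study design and setting, which also describes the blinding, does not clarify these roles.

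**2. Further cue for patients.** Data collection says that app features unlock once the questionnaire is complete. The control program has none to unlock.

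**3. Outcomes by route.** Through the recorder: NIHSS, Barthel, complications (3). Through the patient: BDI-II, EQ-5D-3L, MMAS-8, PSQ (4). Total 3 + 4 = 7, which is every outcome listed in the abstract.

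**4. Scale, under assumption.** Inputs from Study design and setting: Z values 1.96 and 1.282, SD 8 in both groups, means 5 and 12, and 30 per arm before the dropout allowance.

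The plan's own figure first: (1.96 + 1.282)² × (8² + 8²) / (12 − 5)² = 10.51 × 128 / 49 = 27.46. The article gives 27, so its inputs are understood.

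Standard error of a difference in means: 8 × √(2/30) = 2.07 NIHSS points.

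An assumed 1-point differential shift moves z by 1 / 2.07 = 0.48. With no true effect and s = shift / SE, the chance of a two-sided 5% rejection is Φ(s − 1.96) + Φ(−s − 1.96):

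| Assumed shift (points) | s | Rejection probability |
|---|---|---|
| 0 | 0 | 5.0% |
| 1 | 0.48 | 7.7% |
| 2 | 0.97 | 16.2% |
| 3 | 1.45 | 30.6% |

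The shifts are assumptions, and SD 8 is the article's planning value taken from baseline NIHSS. The table shows sensitivity and is not evidence that any bias exists.

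**The case against.** The strongest defence is that the article does take steps at all three levels: a separate installer, patients kept from the other program's content, and coded data with the key withheld. Several stronger readings are tempting and are not supported.

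- **The assessor is unblinded.** A reader might infer this because the rater is the attending neurologist, usual care follows the responsible neurologist, physicians have app accounts (Intervention), and the app offers "the possibility of communicating with the therapist via chats, voice calls or video calls" (Discussion). But nothing says that the rater holds an account or is that contact, and Blinding states that the assessor will not know the group. This remains a risk.
- **The analyst knows the arm from the letters.** The sentence in Blinding can be read as a key, but also as a plain list. Randomization and Data analysis point the other way. Usage duration is the better-founded worry, yet nothing says it reaches the analyst before the between-arm comparison.
- **Patients are told the contrast.** The Discussion says researchers "will fully explain the purposes of the study to them". That concerns consent and does not say the other arm's content is disclosed. The weekly phone calls are not expressly confined to one arm either, so they carry no weight here.
- **The recorder alters scores.** If the neurologist fills out the forms, the recorder may only transcribe ratings already made. That narrows the problem to two sections that disagree about the workflow.
- **All seven outcomes are biased.** Only opportunity is shown.

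What stands after these objections is the arm-aware recorder, the conflict between Blinding and Data collection, and a control app too thin to keep patients blind.

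**Conclusion.** The concern holds in a limited form: triple blinding is not secured by this design. Two parts rest firmly on the text. The installer, who knows the arm, also records the physician-rated results, which does not fit with the neurologist filling out the same forms. And the control app is not a credible sham, so patients who self-report four outcomes can probably infer their arm; that second step is an inference, though a strong one.

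Two parts are weaker. That the attending neurologist learns the arm is a risk on moderate grounds. That the analyst does is uncertain, and depends on how the letters are keyed and when usage data are supplied.

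The documents give no size for any bias. The movement of about 0.5 in z per point of NIHSS rests on an assumed shift, SD 8 and 30 per arm.

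**What to change.** 1. Reconcile Blinding with Data collection: the assessor enters NIHSS, Barthel and checklist scores directly against the study code, and the installer does not record them.
2. Ask patients and caregivers not to mention their app to the assessor.
3. State that the A/B key is drawn at random and kept from the analyst. Release usage data only after the main between-arm analysis is complete.
4. Drop triple blinded from the title and text. Use assessor- and analyst-blinded only if steps 1 to 3 are adopted. Report BDI-II, EQ-5D-3L, MMAS-8 and PSQ as not reliably blinded.
5. Where an existing neurologist who does not treat the patient is available, prefer that person as rater. The article names three neurologists for approving content and the checklist, but does not show that they can act as raters, so this is a preference and not a condition.

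The cost is minor workflow changes and a less favourable blinding label. Sample size and intervention are unchanged. No workflow change makes a questionnaire-only app a convincing sham, so the label needs correcting in any case.
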